## Abstract

**Background::**

The incidence of malnutrition in patients with esophageal cancer is high, which seriously affects the therapeutic effect and quality of life. Oral nutritional supplement is the first choice of nutritional support recommended by current guidelines, which can supplement the lack of energy and protein in patients with esophageal cancer, improve nutritional status and improve the quality of life, but there are few clinical studies. Therefore, the purpose of this randomized controlled trial is to evaluate the effect of oral nutritional supplement therapy on nutritional status and quality of life in patients with esophageal cancer treated undergoing radiotherapy and chemotherapy.

**Methods::**

This is a prospective randomized controlled trial to study the effects of oral nutritional supplement therapy on nutritional status and quality of life in patients with esophageal cancer undergoing radiotherapy and chemotherapy. This study is approved by the Clinical Research Society of our hospital. Patients will be randomly divided into ONS group and traditional diet group. The nutritional status, quality of life score and adverse reactions will be observed before and after radiotherapy and chemotherapy. The data will be analyzed by SPSS 16.0.

**Discussion::**

This study will evaluate the effect of oral nutritional supplement therapy on nutritional status and quality of life of patients with esophageal cancer undergoing radiotherapy and chemotherapy. The results of this experiment will establish clinical evidence for the application of oral nutritional supplement therapy in patients with esophageal cancer undergoing radiotherapy and chemotherapy.

**OSF Registration number::**

DOI 10.17605/OSF.IO/9ZW34.

## Introduction

1

About 40% to 80% of patients with malignant tumors have nutrition-related problems, which are more common in patients with head and neck tumors and digestive tract tumors,^[1]^ and the patients with esophageal cancer have a higher incidence of malnutrition. It is reported that 60% to 85% of patients with esophageal cancer have different degrees of malnutrition, ranking first among all tumors.^[2]^ Malnutrition will affect the therapeutic effect of malignant tumor patients, reduce the quality of life, shorten the survival time, and increase medical expenses.^[3,4]^ According to the guidelines on enteral nutrition for tumor patients issued by the European Society of Enteral and Parenteral Nutrition in 2006, oral nutrition supplement (ONS) is recommended as the first choice of nutritional support for radiotherapy patients.^[5]^ ONS is also recommended as the first choice of enteral nutrition in the consensus of Chinese experts on enteral nutrition for radiotherapy patients with esophageal cancer undergoing radiotherapy.^[6]^

The 2006 European Society for Clinical Nutrition and Metabolism (ESPEN) guidelines unify the English full name of ONS as “oral nutritional supplements” and define it as "supplementary oral intake of foods for special medical uses (formulations) in addition to normal foods.^[7]^ Formula food for special medical purposes is specially processed to meet the special needs of nutrients or diet of people with limited intake, digestive and absorption disorders, metabolic disorders or specific disease status.^[8]^ ONS can supplement the energy and protein in patients with esophageal cancer and improve their nutritional status. At present, this conclusion has been confirmed, but there is a lack of strict randomized controlled trials (RCTs). At the same time, no study has focused on the changes in patients’ quality of life before and after treatment. This study will evaluate the effect of ONS on nutritional status and quality of life in patients with esophageal cancer treated undergoing radiotherapy and chemotherapy.

## Materials and methods

2

### Study design

2.1

This is a prospective RCT to study the effect of oral nutritional supplement therapy on nutritional status and quality of life in patients with esophageal cancer undergoing radiotherapy and chemotherapy. We followed the Consolidated Standards of Reporting Trials (CONSORT) guidelines for reporting randomized trials and provided a CONSORT flow diagram (Fig. 1).

**Figure 1 F1:**
[figure not shown]
Flow diagram.

### Ethics and registration

2.2

This protocol is in line with the Helsinki Declaration and approved by the Clinical Research Ethics Committee of our hospital. This experiment has been registered in the open science framework (OSF) (registration number: DOI 10.17605/OSF.IO/9ZW34). Before randomization, all patients will sign a written informed consent. and they can freely choose whether to continue the trial at any time.

### Patients

2.3

Inclusion criteria:

(1)patients were diagnosed as esophageal cancer, without contraindications of radiotherapy and chemotherapy, planned for radiotherapy and chemotherapy;(2)conscious, able to eat by mouth, volunteer to participate in this clinical study;(3)Nutritional Risk Screening score ≥ 3 (NRS 2002).

Exclusion criteria:

1)patients with unstable vital signs;2)patients with severe stress state, intractable vomiting, and severe diarrhea;3)patients with severe malabsorption syndrome;4)patients with mental or consciousness disorders that could not communicate;5)unable to understand the study plan or unwilling participants after explanation.

### Randomization and blinding

2.4

This study will be randomized into groups without any stratification. Through simple randomization, the patients in the study will be divided into the observation group and the control group according to the 1:1 ratio. Due to the limitation of the intervention in this study, this study cannot achieve strict double-blindness. We will ensure that the study designer, allocators, data analysts, intervention supervisors, and some researchers are blind to personnel allocation.

### Sample size calculation

2.5

This study is a pilot clinical trial. The calculation of the sample size is based on the withdrawal rate of 20% in the clinical study, taking *α* *=* *0.025, power* *=* *90%,* referring to the previous literature.^[9]^ According to the albumin level after radiotherapy, the average score of the test group is 33.3, and the standard deviation is 2.68. The average of the control group is 28.5, and the standard deviation is 3.83. It will be calculated that the minimum number of patients would be included in each group is 25.

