### Statistical analysis

2.9

The data will be statistically analyzed by SPSS 16.0. The counting data will be expressed by rate, $\chi^{2}$ test will be used, and the measurement data will be expressed by $\bar{x}\pm s$. A *t* test will be used for comparison between groups. The difference is statistically significant when *P* < .05.

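### The 25 patients per group in section 2.5 do not follow from its own inputs, which require 13 to 18 per group; 25 per group gives about 99% power, not 90%

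*Protocol article*

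**What the plan says.** Section 2.5 (Sample size calculation) of the protocol article calls the study a pilot trial but bases its size on a formal power calculation. It allows for 20% withdrawal, "taking *α* *=* *0.025, power* *=* *90%,* referring to the previous literature". The assumed outcome is albumin: "According to the albumin level after radiotherapy, the average score of the test group is 33.3, and the standard deviation is 2.68". For the comparator: "The average of the control group is 28.5, and the standard deviation is 3.83". The result is: "It will be calculated that the minimum number of patients would be included in each group is 25".

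Two other sections bear on the calculation. Section 2.4 sets 1:1 allocation. Section 2.9 compares measurement data between groups with a t test and adds: "The difference is statistically significant when *P* < .05". The article gives no formula, no sidedness for alpha and no total sample size.

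**The concern.** Every number needed to repeat the calculation is printed, so the result can be checked without a fuller document. A difference of 4.8 against SDs of 2.68 and 3.83 is a standardised effect of about 1.45. An effect that large needs few patients, and 25 per group looks too many for 90% power.

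This paragraph is the protocol's only quantitative justification for its size. If the result does not follow from the inputs, at least one of three things is wrong: the size, the power, or an input. A reader then cannot say what the trial is designed to detect. The sidedness of alpha adds to this, because section 2.5 uses 0.025 without qualification and section 2.9 tests at .05.

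**Working it through.** **Inputs (section 2.5 unless noted).** Means 33.3 and 28.5; SDs 2.68 and 3.83; alpha 0.025, sidedness not stated, so both readings are tried; power 90%; withdrawal 20%; 1:1 allocation (section 2.4); two-sample t test (section 2.9).

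**Effect size.**
- Difference = 33.3 − 28.5 = 4.8.
- Average variance = (2.68² + 3.83²)/2 = (7.1824 + 14.6689)/2 = 10.926, so pooled SD = 3.305.
- d = 4.8/3.305 = 1.452.

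**Attempt to reproduce 25 per group.** The normal formula is n per group = 2(z_alpha + z_power)²/d². The exact version uses the noncentral t distribution. Enrolment is n/(1 − 0.20), rounded up.

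| Reading of alpha | Method | Evaluable per group | Enrolled per group |
|---|---|---|---|
| One-sided 0.025 (= two-sided 0.05) | Normal: 2(1.960 + 1.282)²/1.452² = 9.97 | 10 | 10/0.8 = 12.5, so 13 |
| One-sided 0.025 (= two-sided 0.05) | Exact t (11 gives 89.9%, 12 gives 92.5%) | 12 | 12/0.8 = 15 |
| Two-sided 0.025 | Normal: 11.77 | 12 | 12/0.8 = 15 |
| Two-sided 0.025 | Exact t (13 gives 89.7%) | 14 | 14/0.8 = 17.5, so 18 |

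A Welch test, which allows for the unequal SDs, gives the same enrolment as the exact t test: 15 and 18. The figure of 25 is not reproduced. It is 1.4 times (25/18) to 1.9 times (25/13) what the inputs require.

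**Conservative variant: SD 3.83 in both arms.**
- Normal formula: 14 evaluable (13.4 rounded up) at one-sided 0.025, so 18 enrolled; 16 evaluable at two-sided 0.025, so 20 enrolled.
- Exact t: 19 enrolled at one-sided 0.025; 18 evaluable at two-sided 0.025, 18/0.8 = 22.5, so 23 enrolled.

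The range is 18 to 23, which is still short of 25, and it sets aside the stated SD of 2.68.

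**What 25 per group delivers.** Evaluable per group = 25 × 0.8 = 20. Exact t power for a difference of 4.8, pooled SD 3.305:
- two-sided 0.05: 99.4%;
- two-sided 0.025: 98.6%.

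With SD 3.83 in both arms, the same 20 per group give 97.1% and 94.4%. At two-sided 0.05 and pooled SD 3.305, 20 per group have 90% power for 1.052 SD = 1.052 × 3.305 = 3.48, about 3.5 in the same albumin units.

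**Two routes that do lead to 25.**
- As a total for both arms: 2 × 10/0.8 = 25. This works only with the normal formula at one-sided 0.025; the other three rows of the table give totals of 30 to 36.
- As a per-group number with a variance slip: adding the two variances instead of averaging them doubles 9.97 to 19.93, so 20, and 20/0.8 = 25.

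The arithmetic does not favour one route over the other.

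**The case against.** The strongest reply is that the error does no harm. The text says 25 in each group, and with 1:1 allocation that means 50 patients. On that basis the trial exceeds its stated power with room to spare. The article also calls the study a pilot, where a size above the formula's result is easy to defend. This stands, and it sets the severity. It does not rescue the sentence, which presents 25 as the calculated minimum for 90% power.

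A second reply is that a cautious choice of SD could explain the figure. The larger SD with a t test at two-sided 0.025 gives 23, two short of 25. A conservative choice cannot be excluded, but the article states both SDs and mentions no such choice.

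A third reply is that the two significance levels are compatible, because one-sided 0.025 is the same test as two-sided 0.05. That is correct. The levels conflict only if 0.025 is two-sided, so this is a point to clarify and not an established contradiction.

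In the other direction, a reader might infer from 2 × 10/0.8 = 25 that the sponsor reported the two-arm total as a per-group number, and that the trial is underpowered. With 25 patients in all and 10 evaluable per arm, exact t power would be 86.7% at two-sided 0.05 or 78.1% at two-sided 0.025. The document does not support this. It says each group, gives 25 nowhere as a total, and the variance slip explains the figure equally well.

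**Conclusion.** The point holds as an error of arithmetic and reporting, of moderate severity. From both stated SDs, the inputs in section 2.5 require 13 to 15 per group at one-sided 0.025 and 15 to 18 at two-sided 0.025, against 25 stated. At 25 per group the power for a difference of 4.8 is about 99%, not 90%.

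This rests on equal allocation, a two-sample comparison of post-treatment albumin, and withdrawal handled by dividing by 0.8. It does not depend on the reading of alpha or on the choice between normal, t and Welch formulas, since none of them reaches 25. The origin of the figure remains unknown. The discrepancy is on the safe side, and underpowering is not shown.

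**What to change.** Confirm that 25 is the number per group, so 50 in total. If so, keep it and correct the description around it:

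- Remove the word minimum.
- Name the formula and state the sidedness of alpha. If one-sided 0.025 was meant, write it as two-sided 0.05 so that it matches section 2.9. If two-sided 0.025 was meant, quote 98.6% power below and bring section 2.9 into line.
- Restate the power, for example:

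> With 25 patients per group (50 in total) and 20% withdrawal, 20 evaluable patients per group give about 99% power at two-sided alpha 0.05 to detect a difference of 4.8 in albumin after radiotherapy, assuming SDs of 2.68 and 3.83.

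Optionally, add that this size has 90% power at two-sided 0.05 for a difference of about 3.5 in the same units. That figure describes the design. It is not a new target, since the article supports no target other than 4.8.

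The cost is one rewritten paragraph, with no extra patients. If the sponsor answers that 25 was meant as the total, the power statement must be recalculated on that basis before it is restated.

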### Intervention measures

2.6

After the beginning of the study, dietitians will give one-to-one nutrition education to the two groups of patients once a week, investigate the results of patients’ dietary intake, give nutritional guidance and formulate dietary recipes according to different conditions, and issue a diet guidance sheet for cancer patients at the same time.

In this study, patients in the control group will not be given ONS supplement. We will set up the Nutrition Support Steam to provide comprehensive nutritional care for patients in the experimental group,^[10]^ refer to the recommendation of enteral nutrition guidelines made by ESPEN,^[11]^ and make rational use of ONS for a nutritional supplement to achieve the purpose of nutritional treatment. According to the clinical nutrition diagnosis and treatment process, the nutrition support group carries on the screening, evaluation, nutrition support plan formulation, implementation, monitoring, and program adjustment. The target nutritional feeding amount was determined as follows: total energy supply was 125 to 146 KJ/ (Kg·d) and protein 1.2 to 1.5 g/ (Kg·d). Nutrition is based on the 5-step treatment principle of malnutrition,^[12]^ the individualized diet plan is made according to the different conditions of patients every day and various laboratory indicators, and the tumor total nutrition formula food is used for ONS to achieve the target requirement. The implementation of the program will begin 3 days before radiotherapy and chemotherapy.

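### The arms differ by nutrition-support-team care as well as by ONS, so the comparison cannot support a conclusion about ONS alone

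*Protocol article*

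**What the plan says.** The first paragraph of section 2.6 describes care common to both arms: "dietitians will give one-to-one nutrition education to the two groups of patients once a week". The same dietitians survey intake, give guidance, draw up recipes suited to the patient's condition and hand out a diet guidance sheet.

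The second paragraph separates the arms. For the control arm it says only that "patients in the control group will not be given ONS supplement". For the other arm it says: "We will set up the Nutrition Support Steam to provide comprehensive nutritional care for patients in the experimental group" (the context shows that a support team is meant). This team is responsible for the whole nutrition process, up to monitoring and adjusting the programme. The paragraph goes on to give energy and protein targets, says that "the individualized diet plan is made according to the different conditions of patients every day and various laboratory indicators", and names formula food as the ONS used to reach the target.

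The purpose is worded differently. The Introduction says "This study will evaluate the effect of ONS on nutritional status and quality of life in patients with esophageal cancer", after defining ONS as formula food taken in addition to ordinary food. The abstract's Methods describe the allocation thus: "Patients will be randomly divided into ONS group and traditional diet group". The abstract's Discussion says "This study will evaluate the effect of oral nutritional supplement therapy on nutritional status and quality of life of patients with esophageal cancer", and then: "The results of this experiment will establish clinical evidence for the application of oral nutritional supplement therapy". Section 3 repeats the aim and lists two limitations: incomplete blinding and a regional population.

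**The concern.** Randomisation supports a causal reading of everything that differs between the arms, taken together. If only ONS differed, a difference in albumin, intake or SF-36 could be credited to ONS. Here one arm also gets a team that plans, monitors and adjusts its nutrition. Such care could plausibly change intake, body mass and blood proteins through ordinary food. It could also change SF-36, which patients report themselves and which section 3 concedes is not collected under strict double-blinding.

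What is at stake is the conclusion. Even a clearly positive result would not show that the supplement produced it. A hospital that adopted ONS without the team could not rely on this trial to expect the same benefit.

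**Working it through.** The plan gives no figure on this point to reproduce, so the check compares the text for the two arms.

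| Element | Control arm | Experimental arm | Where |
|---|---|---|---|
| NRS 2002 score of at least 3 | yes | yes | 2.3, inclusion criterion 3 |
| Weekly one-to-one education, intake survey, guidance, recipes by condition, guidance sheet | yes | yes | 2.6, first paragraph |
| Weekly dietary survey and body mass; data every two weeks | yes (no limit to one arm) | yes | 2.7, 2.8 |
| Support team: plan formulation, implementation, monitoring, adjustment | not described | yes | 2.6, second paragraph |
| Individual plan that also uses laboratory indicators | not described | yes, by position in the team paragraph | 2.6, second paragraph |
| Energy and protein targets | arm not named | likely, by position in the team paragraph | 2.6, second paragraph |
| ONS | no | yes | 2.6, second paragraph |

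**Step 1: what differs for certain.** Two rows differ on express wording: ONS, and the support team with its planning, monitoring and adjustment. The laboratory-based plan and the targets probably differ too, but the argument does not need them.

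**Step 2: what the analysis estimates.** Section 2.9 plans a t test between groups for measurements and a chi-squared test for counts. For any outcome, the expected difference between arms is

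difference = effect of ONS + effect of team care + any interaction of the two.

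Two arm means yield one difference, and there are at least two unknowns on the right. No arm has the team without ONS, or ONS without the team, so the terms cannot be separated.

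**Step 3: whether size helps.** More patients reduce the standard error of the left-hand side and leave the right-hand side as it is. Section 2.5 plans on albumin means of 33.3 and 28.5, a difference of 33.3 − 28.5 = 4.8. If 4.8 were observed, it would be the total for the package, at any sample size. The planning values come from earlier literature whose intervention is not described here, so they do not help to divide it.

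**Step 4: what is claimed.** The Introduction defines ONS as a product and asks for its effect. The abstract's Background, Methods and Discussion, section 2.1 and section 3 speak of oral nutritional supplement therapy. None of them names the team as part of what is being tested, and section 3 does not list it as a limitation.

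**The case against.** The strongest reply is that oral nutritional supplement therapy, the wording used in most places, can fairly mean ONS as delivered. An individually dosed supplement needs a target, follow-up and adjustment, and the team is how it is given. Comparing that strategy with weekly counselling is a legitimate trial. This stands, and it is why the design need not change. It does not rescue the Introduction, which defines ONS as the formula food and asks for the effect of ONS itself. If the package was meant, the protocol should say so.

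A second reply is that the arms are closer than they first appear. This also stands in part. A reader might infer that the control arm has no screening, evaluation or monitoring. The text does not support that: NRS 2002 screening is an entry criterion for all, and the weekly survey, weekly body mass, guidance and condition-based recipes are not confined to one arm. The imbalance lies in the team's organised planning, monitoring and adjustment on top of these.

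Two further inferences are tempting and not secure:

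- **Daily against weekly contact.** In the sentence on the individual plan, the reference to every day may belong to the patients' condition rather than to the making of the plan. Daily planning would in any case not be daily contact, and no contact frequency is given for the team.
- **Targets for one arm only.** The targets stand in the experimental-arm paragraph, but the sentence names no arm.

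That a journal article condenses the protocol is no answer. The point rests on two things the article states, a team for one arm and an attribution to ONS, and not on something it leaves out.

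**Conclusion.** The point holds. The trial as described estimates the effect of nutrition-support-team care including ONS, compared with weekly dietitian counselling without ONS. The stated question and conclusion about ONS go beyond that, and the limitations do not say so.

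No size can be given. A reader might want to state what share of a difference could be due to the team, but the documents support no such figure; they show only that the share is not identified. Nor does it follow that the trial is invalid: the randomised comparison of the two packages of care is sound on this point, and the fault lies in the attribution.

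The conclusion rests on one assumption: that the control arm receives no equivalent team care. The article sets up the team for the experimental group and describes none for the control group.

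**What to change.** Restate the objective and conclusion as the effect of nutrition-support-team care including ONS versus weekly dietitian counselling without ONS. The places are the abstract (Background, Methods, Discussion), the Introduction, section 2.1 and section 3. Add to the limitations in section 3 that the arms differ by team care as well as by ONS, so the effect of ONS alone is not identified. Say in section 2.6 whether the intake targets apply to one arm or to both.

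This changes wording only: no patients, visits or measurements are added. The cost is a narrower claim, less specific to the product. If the control arm's label is revised at the same time, it could mention the weekly counselling, but that is minor.
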